#### Assessing the impact of the novel pathway on diagnosis rates of advanced liver fibrosis compared with usual care

To assess the impact of the pathways for identifying new cases of advanced fibrosis, a comparison of rates of identification of new cases of advanced fibrosis will be conducted in the participating practices in preceding years (avoiding COVID-19 as a confounder). Rates of advanced fibrosis will be determined by the number of patients (age 18–80 years) referred to secondary care gastroenterology/liver services in the period who received a diagnosis of advanced fibrosis/cirrhosis. Regional guidelines recommend that patients with suspected advanced fibrosis/cirrhosis are referred to secondary care,^36^ so this methodology should identify those new diagnoses.

The number of new diagnoses of advanced liver fibrosis/cirrhosis will be assessed in four control practices that have similar demographics and clinical management over the study period to determine rates of diagnosis of advanced fibrosis/cirrhosis diagnosis by current clinical pathways.

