## Introduction

Undiagnosed fatty liver disease is highly prevalent in the community, primarily due to high rates of harmful alcohol consumption and/or obesity.^1^ Fatty liver disease can progress to cirrhosis and complications including liver failure and hepatocellular carcinoma. An estimated 1-in-5 individuals in the UK have non-alcohol-related fatty liver disease (NAFLD).^2^ Moreover, the prevalence of potentially harmful alcohol consumption is high in the community (15% females and 25% males in England) and alcohol accounts for 75% of deaths due to liver disease, costing the National Health Service (NHS) £3.5 billion per annum.^1^ The increasing prevalence of liver disease risk factors in the community and lack of recognition of liver disease are likely causes for the rising rates of cirrhosis and liver-related deaths.^1^

Because liver disease is usually asymptomatic at early stages, patients frequently present once end-stage liver disease has developed. One study showed that 73% of patients presenting with their first admission with cirrhosis or liver failure had never been referred to a liver clinic, which indicates a lack of early detection of liver disease.^1^ Importantly, most liver-related complications, mortality, healthcare costs and reduction in quality of life occurs in patients with cirrhosis rather than earlier stages of liver disease.^3 4^ Therefore, early identification of liver disease before cirrhosis and initiation of lifestyle changes may prevent progression to cirrhosis for some patients.^5^

Liver enzymes are often used in primary care to identify individuals with liver disease,^6^ but this approach is insensitive because up to 50% of patients with advanced liver fibrosis/cirrhosis have normal liver enzymes.^7^ Because stage of liver fibrosis is the key prognostic factor in liver disease,^8^ use of a test for fibrosis is likely to be far more efficient to identify advanced fibrosis. Therefore, taking a different approach and performing case finding using non-invasive tests to identify advanced liver fibrosis in individuals with liver disease risk factors may be an effective strategy.^9 10^

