#### Secondary outcomes

Assess the utility of non-invasive testing/triage strategies to identify patients who have liver-related events (death, hepatic decompensation and transplantation) during longitudinal follow-up at 2, 5 and 10 years via electronic care records/NHS Digital.Compare the number of new cases of advanced fibrosis/cirrhosis identified with previous years in participating practices and control practices historically and over the study period.Assess the performance of FIB-4, ELF, PRO-C3 and other novel blood-based biomarkers alone or in combination to identify advanced fibrosis/cirrhosis as defined by overall clinical assessment or LSM.Assess the performance of the biomarkers to correctly exclude advanced fibrosis/cirrhosis.Assess the uptake of the liver assessment, attendance rates for VCTE and liver clinic appointments with both pathways.Conduct a subsequent cost effectiveness analysis of established and novel pathways.Assess barriers and facilitators to incorporating the pathway into routine primary care practice.Development of the optimum pathway (clinically and cost-effective and implementable) for further evaluation.

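### The usual-care count of new advanced fibrosis in preceding years rests on specialist referral and may miss diagnoses made without one, so the gain over usual care may be overstated, chiefly as a ratio

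*Protocol article*

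**What the plan says.** The protocol article's second specific aim asks whether the pathways increase diagnosis of advanced fibrosis compared with standard care. The matching item under Secondary outcomes reads: "Compare the number of new cases of advanced fibrosis/cirrhosis identified with previous years in participating practices and control practices historically and over the study period".

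The section on the impact of the novel pathway compared with usual care sets out the method. For participating practices, "a comparison of rates of identification of new cases of advanced fibrosis will be conducted in the participating practices in preceding years", leaving out the COVID-19 period. The case rule is "Rates of advanced fibrosis will be determined by the number of patients (age 18–80 years) referred to secondary care gastroenterology/liver services in the period" who then received a diagnosis of advanced fibrosis or cirrhosis. The argument for completeness is that "Regional guidelines recommend that patients with suspected advanced fibrosis/cirrhosis are referred to secondary care", "so this methodology should identify those new diagnoses". For the comparison practices the section says "The number of new diagnoses of advanced liver fibrosis/cirrhosis will be assessed in four control practices", over the study period, and does not repeat the referral rule.

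The Introduction makes the case for active case finding partly on this evidence: "One study showed that 73% of patients presenting with their first admission with cirrhosis or liver failure had never been referred to a liver clinic".

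Under Study procedures, participants with a liver stiffness above 8 kPa are referred to secondary care as part of the study.

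**The concern.** The argument for completeness relies on what a guideline recommends, not on observed referral practice. The article's own background evidence suggests that, among people who reach hospital with cirrhosis or liver failure, earlier referral is the exception. A usual-care diagnosis that first arises at an admission, or is only coded in the practice record, enters the count only if a referral to gastroenterology or liver services also occurs in the period. The text does not say whether such cases are otherwise counted.

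The shortfall would not fall evenly. Pathway cases meet the referral criterion because the protocol refers them. A person who would otherwise have been diagnosed at an admission in the same period can become a counted referral under the pathway while staying uncounted under usual care. A change of diagnostic route would then look like an additional diagnosis.

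A smaller point affects the same comparison. Secondary outcomes lists control practices historically and over the study period, while the analysis section describes them over the study period only. Without historical control counts, the before–after change in participating practices has no change in controls to set beside it.

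At stake is the answer to the second specific aim. The primary outcome and the biomarker accuracy analyses are not affected.

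**Working it through.** **No figure to reproduce.** The article gives no usual-care rate, effect size or power for this comparison, so what follows is a sensitivity calculation.

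**Inputs**
- u = 0.73: share never referred before a first admission with cirrhosis or liver failure (Introduction, one cited study).
- s: share of all usual-care new diagnoses first made at such an admission. Not in the documents; assumed.
- c: share of those never-referred patients who are referred after the admission, within the period, and so are counted. Not in the documents; assumed.

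**Formulas**
- Fraction of usual-care diagnoses missed: m = u × s × (1 − c).
- Inflation of the rate ratio when only the usual-care count is incomplete: 1/(1 − m).

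**Worked case, c = 0 (the largest effect through this route)**
- s = 20%: m = 0.73 × 0.20 = 0.146; 1/(1 − 0.146) = 1.17.
- s = 50%: m = 0.73 × 0.50 = 0.365; 1/(1 − 0.365) = 1.57.

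**Range over s and c**

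| s (assumed) | c = 0 | c = 50% | c = 90% | c = 100% |
|---|---|---|---|---|
| 20% | 1.17 | 1.08 | 1.01 | 1.00 |
| 25% | 1.22 | 1.10 | 1.02 | 1.00 |
| 50% | 1.57 | 1.22 | 1.04 | 1.00 |

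For example, s = 50% and c = 90% gives m = 0.73 × 0.50 × 0.10 = 0.0365 and 1/(1 − 0.0365) = 1.04.

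**Ratio versus difference.** Take, for illustration only, T = 50 true usual-care diagnoses, P = 150 extra pathway diagnoses, s = 25% and c = 0. The referral rule counts R = 50 × (1 − 0.1825) = 40.9.
- True values: ratio (150 + 50)/50 = 4.00; difference 150.
- Same rule in both periods, with unreferred admissions equally frequent: ratio (150 + 40.9)/40.9 = 4.67; difference still 150.
- Only the usual-care count incomplete: ratio 200/40.9 = 4.89; difference 200 − 40.9 = about 159.

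The ratio moves in both cases. The difference moves only if the shortfall differs between periods, for instance when the pathway turns would-be admissions into referrals.

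**The case against.** The strongest reply is that the two statements can both be true. The 73% describes referral before a first admission. The counting rule asks for a referral in the period and does not say that it must precede an admission or come from a general practitioner. A patient diagnosed on a ward and then referred to hepatology in the same period is counted. This stands, and it is why the inflation may be close to 1.

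A reader might infer that 73% of usual-care diagnoses are lost, or that the gain is certainly overstated. The documents support neither. The percentage applies to a subset of patients in one study, the admission share is an assumption, and the inflation range begins at 1.00.

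Three further points on the other side also hold. The referral rule is explicit only for the preceding-years comparison, so it should not be read as settled for the control practices. Secondary outcomes already plans historical control counts, so it would be wrong to call the design an uncontrolled before–after study; the analysis section is simply less complete. The list-size denominator and the regression model are matters for the analysis plan. Nor does the article say that the hepatologist panel's staging will be used in this comparison.

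What the reply does not remove is that completeness is asserted from a recommendation alone, the background evidence points the other way, and the treatment of diagnoses made without a referral is left open.

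**Conclusion.** The point holds as a likely, not a proven, under-count. The stated rule can miss usual-care diagnoses made at admission or recorded without a referral, while pathway cases satisfy it by protocol. The plausible direction favours the pathway, mainly on the ratio scale; the absolute difference need not change if the same rule and the same rate of unreferred admissions apply in both periods.

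The size cannot be settled from the documents. Through the admission route, the bound is 1/(1 − 0.73s). It assumes that the cited 73% carries over to these practices and that none of the never-referred patients is later counted. Diagnoses recorded only in primary care would add to the shortfall, but the article gives no figure for them.

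This bears on one secondary outcome and deserves correction before the counts are extracted.

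**What to change.** In the section on impact compared with usual care:

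1. Define a new diagnosis as the first recorded advanced fibrosis or cirrhosis at age 18–80 from any of three sources: specialist referral, hospital admission or primary care code.
2. Apply that one rule, using the routine diagnosis, to participating and control practices and to both the preceding years and the study period.
3. State that the four control practices are counted historically as well as over the study period, in line with Secondary outcomes, so that the change in participating practices can be compared with the change in controls.

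The cost is a broader search of practice and hospital records. The historical control extraction is already implied by the secondary outcome. The downside for the study is that the apparent gain over usual care may shrink.

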### Specific aims

To implement and assess the effectiveness of primary care-based risk-stratification pathways using VCTE and blood biomarkers to identify advanced liver fibrosis and predict outcomes among individuals with liver disease risk factors.To evaluate whether implementation of the pathways increases the diagnosis of patients with advanced fibrosis compared with standard care.To use the Stratification Of LIver Disease (SOLID) platform to assess the performance of novel and established fibrosis biomarkers and so determine the optimum biomarker strategy for wider implementation within the NHS.To assess the cost effectiveness of novel and established risk stratification pathways.To assess the acceptability of embedding the pathways into routine primary care chronic disease management to guide wider implementation.

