### Inclusion criteria

Individuals aged 18–80 years attending for an ‘annual review of care’, ‘chronic disease review’ or ‘health check’ with one or more of the following risk factors:

Obesity (BMI>30 kg/m^2^).T2DM.Potentially hazardous/harmful alcohol consumption (AUDIT score>8).^33^

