#### Sample size calculation and power estimates

This study will recruit 3000 participants from Primary Care Networks in Northeast England. Searches in two practices indicate that at least 2600 of 20 000 patients meet the eligibility criteria and attend annual year of care reviews. In addition, approximately 200 patients attend 5-yearly health reviews. Approximately 1500 patients will be recruited into each pathway. We estimate that the prevalence of moderate/advanced fibrosis in the recruited population will be 5%–7.5%.^9 39 40^

With a prevalence of advanced fibrosis of 5%–7.5%, this will give us 150–225 true positives and 2775–2850 true negatives. The large sample of true negatives will result in higher precision to estimate specificity than sensitivity. The total sample size of 3000 will provide a precise estimate of the true prevalence for this population. If the true prevalence is 5%–7.5%, the expected width of the 95% CI for the population prevalence is 0.06–0.019.

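### The comparison with usual care fixes no common population, denominator or referral-to-diagnosis window, so the pathway's gain could come out diluted, understated or overstated

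*Protocol article*

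**What the plan says.** The second item under Specific aims in the protocol article asks "whether implementation of the pathways increases the diagnosis of patients with advanced fibrosis compared with standard care". The matching item under Secondary outcomes is to "Compare the number of new cases of advanced fibrosis/cirrhosis identified with previous years in participating practices and control practices historically and over the study period".

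The method is in the section on the impact of the pathway on diagnosis rates. There, "a comparison of rates of identification of new cases of advanced fibrosis will be conducted in the participating practices in preceding years", avoiding the COVID-19 period. A rate is determined by the "number of patients (age 18–80 years) referred to secondary care gastroenterology/liver services in the period who received a diagnosis of advanced fibrosis/cirrhosis". New diagnoses also "will be assessed in four control practices that have similar demographics and clinical management over the study period".

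Under Inclusion criteria, the pathway is open only to people aged 18–80 who attend a review or health check "with one or more of the following risk factors": BMI above 30, type 2 diabetes, or an AUDIT score above 8. Known liver disease under secondary care follow-up is an exclusion. The sample size section reports a search of two practices in which a minimum of 2600 out of 20 000 "patients meet the eligibility criteria and attend annual year of care reviews", with about 200 more at five-yearly health reviews. Recruitment runs from 31 October 2022 to 31 August 2024 (Ethics and dissemination).

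**The concern.** The usual-care case definition takes the age band from the entry criteria and leaves out the risk-factor condition. Someone aged 18–80 with none of the three risk factors who is referred and found to have cirrhosis from another cause is a usual-care case, yet could never have entered the pathway.

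Two further elements are open. The text speaks of rates but defines them by a number of patients, with no denominator. It also does not say whether the study-period side is every such referral from participating practices or only the cases found through the liver health check. Without these, a reported gain over usual care cannot be read as a pathway effect.

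The definition also places a case in a period by its referral and sets no limit on when the diagnosis must follow. Referrals from earlier years have had longer to become diagnoses than those made near the end of recruitment.

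At stake is the answer to the second specific aim and one secondary outcome. The primary outcome is not affected.

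**Working it through.** **The plan's own figure.** The article gives no expected usual-care count and no power for this comparison. The nearest figure, the expected yield of the cohort, reproduces: 3000 × 0.05 = 150 and 3000 × 0.075 = 225.

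**Inputs from the article.** Eligible share of the list, E/L: 2600/20 000 = 13%, or 2800/20 000 = 14% with the health-review attenders. Inverted, L/E = 7.69 and 7.14.

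**Assumed inputs (not in the article).**
- P = study-period cases in the risk-factor population = 100.
- U = usual-care cases aged 18–80 over a comparable period = 20.
- f = share of U that the pathway could not reach = 20%, so fU = 4 and (1 − f)U = 16.
- The out-of-reach cases continue at fU during the study period.

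**Four ways to make the comparison.**

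| Count used | Difference | Ratio |
|---|---|---|
| Eligible patients on both sides | P − (1 − f)U = 100 − 16 = 84 | 100/16 = 6.25 |
| All adults 18–80 on both sides | (P + fU) − U = 104 − 20 = 84 | 104/20 = 5.2 |
| Pathway cases against all referrals | P − U = 100 − 20 = 80 | 100/20 = 5.0 |
| Pathway cases per eligible patient against usual care per listed patient | not on one scale | (100/2600)/(20/20 000) = 38.5 |

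**What follows for other values.**
- Second row: (P + fU) − U equals P − (1 − f)U whatever the inputs, so the absolute difference is unaffected. With R the eligible-only ratio, the all-adult ratio is R(1 − f) + f, which is pulled towards 1 but does not cross it.
- Third row: the difference falls short by fU. For U from 10 to 40 and f from 10% to 30%, that is 1 to 12 cases; it is 0 if f = 0. The ratio becomes R(1 − f).
- Fourth row: the ratio is P/U multiplied by L/E, an inflation of 7.1 to 7.7 times over the third row. Against the eligible-only ratio the factor is (1 − f) × L/E = 0.8 × 7.69 = 6.15. This overstates the gain unless f exceeds 1 − E/L, which is 86%–87%. The 7.1–7.7 is an upper guide: 2600 is a minimum, and the 20 000 are not said to be limited to ages 18–80.

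**Timing.** Recruitment lasts 22 months. If records were searched at its close (an assumption), a referral on the first day would have had 22 months to become a diagnosis and one on the last day none, while every referral from preceding years would have had more than 22 months. Assessment after referral includes secondary care work-up, sometimes biopsy, and a judgement by three hepatologists. Control practices are counted over the same study period, so their referrals face the same spread. The size of the historical imbalance cannot be calculated, because the article gives no referral-to-diagnosis interval.

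**The case against.** The strongest reply is that the secondary outcome describes a practice-level count across periods and practices. On that reading one definition serves everywhere, out-of-reach diagnoses appear on both sides, and they cancel in the difference. This stands. Only a ratio is diluted, and the article does not commit to a ratio.

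Nor does the second specific aim itself limit the question to people with risk factors. Whole-practice yield is a legitimate target, and a smaller whole-practice ratio is then simply the whole-practice effect. This also stands, and is why the all-adult count should be kept.

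Restricting to recorded risk factors has its own hazard. In the study, participants enter their AUDIT score at consent, whereas past and control records hold only what routine care coded. Alcohol-related cases could drop out of the comparator alone and inflate the gain. That is a good reason not to make the restricted count the only one.

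On timing, the words about the period might be meant to bound the diagnosis as well as the referral, and a condensed article can leave the data-cut rule to the full protocol. But the sentence as published ties the period to referral and is offered as the case definition. The control practices' similar demographics and management help the concurrent comparison; they do not settle the denominator or the historical follow-up.

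**Conclusion.** The point holds as a mismatch with undetermined direction. The usual-care definition applies the age limit only, no common denominator is named, and time from referral to diagnosis is unlimited. On the illustrative inputs the ratio runs from 5.0 to 38.5 against an eligible-only value of 6.25, and the difference is 80 or 84. P, U and f are assumptions.

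A reader might infer more, and the documents do not support it:
- That the gain over usual care is necessarily understated. This follows only if pathway cases are set against all referrals on raw counts or a common denominator.
- That 86%–87% of usual-care diagnoses are out of reach because 13%–14% of the list is eligible. That is a share of patients on the list and says nothing about the share of diagnoses.
- That a true doubling would look like a loss. This needs the pathway-against-all-referrals reading and an assumed f of 60%: 2 × 0.4 = 0.8. With all adults on both sides the same inputs give 2 × 0.4 + 0.6 = 1.4.

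The timing element has a direction: it favours the historical comparator and so works against the pathway. It does not touch the comparison with concurrent control practices.

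**What to change.** 1. Apply one case definition and one denominator to participating practices (preceding years and study period) and to control practices. Keep the all-adult 18–80 count on both sides, and say that the study-period side is counted in the same way. Beside it, report the count restricted to patients with recorded BMI above 30, type 2 diabetes or hazardous alcohol use who are not already under liver follow-up, over the matching denominator. Add a sensitivity analysis on BMI and type 2 diabetes only, because alcohol recording may be the least complete.
2. In every period and practice, count a diagnosis only if it is made within the same fixed interval from referral, for example 12 months.

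The cost is wording, plus running the eligibility search already used for the sample size in the comparison years and the four control practices. With a 12-month interval and referrals counted to 31 August 2024, the final extraction could not be made before 31 August 2025. The downsides are incomplete past alcohol coding in the restricted count and slightly fewer cases counted overall.
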